### **Inside model selection**

To find the optimal hyper-parameters (not features/variables to use) for each model (except multiple linear - / Cox regression as they do not have hyper-parameters) **Random Grid Search Cross Validation** will be used. As this technique is able to identify near optimal parameters in reasonable time.

### ***Identification of relevant circulating biomolecules as risk factors***

To identify the circulating biomolecules that can be used as robust explanatory variables i. e. risk factors **permutation feature importance [1]** will be used as it is a model agnostic technique.

## Data preprocessing

### Categorical variables

The categorical variables are all dichotomous therefore no grouping is applied. All categorical variables will be one-hot-encoded i.e. **dummy variables** will be created.

### Numerical variables

Numerical variables will be **normalized** before being fed into the models for training and testing. Also log-transformation of numeric variables will be applied. As these transformations are crucial for the success of Algorithms that rely on stochastic gradient decent like artificial neural networks, they are not necessary preprocessing steps for tree-based models.

We are going to apply these transformations anyway to compare their impact on the prediction power.

### All variables

A 20 % **hold-out dataset** will be used for evaluating the final model that only relies on the most relevant variables and has been trained on the remaining 80 % of the dataset. At model training time the training set will be further split into **k-fold-cross validation** datasets. The split will be **stratified** for the dependent variable.

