#### **Analysis Population**

The EAST – AFNET 4 study offered all participants participation in a biosample sub-study. Due to regulatory delays, this offer could not be made to the first 399 patients. The analysis population will consist of all patients randomized in the EAST – AFNET 4 trial in whom biosamples were collected.

For comparison of the effect of the randomized intervention, early rhythm control, we will compare intention to treat populations as a primary analysis.

The analysis population will include those patients from the original study who agreed to also contribute to the circulating biomolecules sub-study. These are 1586 patients of which approximately 50% are women and also around 50% received usual care against about 50% that received early treatment.

We will compare clinical characteristics of the sub-study population with the patients not participating in the sub-study to identify potential differences.

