#### **Aim of the study**

The study aims to identify circulating biomolecules associated with the **severity level of heart disease**. Promising candidate circulating biomolecules were identified using a modified Delphi approach. Details have been published, [7], [8], [9]. For this purpose, different multivariate analyses are performed. In addition, different machine learning (ML) models will be used to predict the **dependent variables**:

- **1st co-primary outcome** – which is a composite of the variables:

- cardiovascular death
- stroke / transient ischemic attack
- hospitalization
  - due to worsening of heart failure or
  - due to acute coronary syndrome

is a time-to-event endpoint consisting of:

- a categorical, nominal scaled variable that can take the two expressions true or false  
and
- the time from admission of the participant in the study till observation of the event.

- **2nd co-primary outcome** – 'nights spend in hospital per year'

is a numeric, discrete scaled variable that ranges from 0 to  $n$  number of nights. We will add one night to each value to enable log transformation in addition to using the collected number of nights spent in hospital.

- **Primary safety outcome** – which is a composite of death, stroke, and serious adverse events of rhythm control therapy.

To increase power and to explore the effect on all events, recurrent events will be analyzed in a separate analysis. In addition, circulating biomolecules predictive of components of the primary outcome will be analyzed. We will also determine biomolecule concentrations associated with the primary safety outcome, its components, and biomolecule concentrations associated with major bleeding (captured as SAE). To determine factors that affect the primary outcome, we plan an extended multivariate analysis including clinical parameters associated with the primary outcome (see Kirchhof et al NEJM 2020, supplementary data and Metzner et al Europace 2021) and biomolecule concentrations.

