## EAST-AFNET circulating biomolecules sub-study

- **Specific hypotheses.** Based on our biomedical knowledge, we developed specific hypotheses that will be tested in the EAST – AFNET 4 biomarker sub-study. These include the following:
  1. BMP10 concentrations are associated with recurrent AF and affect recurrent AF differentially depending on the use of sodium channel blockers (flecainide, propafenone).
  2. FGF23 concentrations are associated with recurrent AF.
  3. A combination of ANG2, FGF23, and BMP10 predicts recurrent AF better than natriuretic peptides.
  4. ESM1 concentrations are associated with stroke (both prior stroke at baseline and future stroke during FU) and with the composite of stroke and cardiovascular death
  5. The ABC bleeding score is associated with major bleeding
  6. The ABC stroke score is associated with stroke and with the composite of stroke and cardiovascular death
  7. BNP is associated with heart failure hospitalizations and with the composite of death or heart failure hospitalization
  8. Angiotensin 2, FGF23 (alone or in combination or in combination with ESM1) are strong predictors for stroke or stroke and ACS, or stroke + ACS + CV death

- The 14 circulating biomolecules:
  - ANG2
  - BMP10
  - Cancer-Antigen 125 (CA-125)
  - Cardiac C-Reactive Protein High Sensitive
  - Creatinine (enzymatic determination)
  - D-Dimer [Explicit units would be "ug FEU/mL]
  - ESM1
  - FBP3
  - FGF23
  - Growth Differentiation Factor-15
  - Interleukin-6
  - IGFBP7
  - NT-proBNP
  - Troponin T high sensitive (cTnT-hs)

all numeric, continuous scaled

To enable evaluation of these circulating biomolecules in context with clinical information, a list of parameters that are associated with the primary outcome will be included in the analysis. A preliminary list will be taken from the existing analyses in the trial. If there are too many candidates, we will do some variable reduction to discard “redundant” variables without using the association with the endpoints to inform that decision (e. g. correlations, PCA, etc.).

See supplement to the main results publication for a list of preselected parameters.

- additional **clinical** parameters collected at baseline:
  - age
    - numeric, discrete scaled
  - gender
    - categorical, nominal scaled – dichotomous
  - random group
    - categorical, nominal scaled – dichotomous
- BMI
  - numeric, continuous scaled
- Heart Failure, determined using heart failure symptoms and LVEF

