### **Inference Analytics**

It is expected that clinical parameters and biomolecule concentrations will interact in complex ways. These multiple interactions are not well captured by classical regression analyses. On the other hand, multiple regression remains the 'gold standard' in the field. To reflect these complexities and demands, we will train four types of models separately for the 1st primary outcome, the 2nd primary outcome, and the primary safety outcome. Those model types include statistical learning (SL), machine learning, and deep learning (DL) approaches. Furthermore, each of the  $3 * 4 = 12$  models will be trained with clinical confounders and with clinical confounders combined with circulating biomolecules. This gives us the ability to eventually compare 24 models and their reflection of interactions between the clinical parameters and biomolecule concentrations.

- A time-to-event machine learning problem to be solved by different candidate models to be compared against each other. These are namely:
- For 1st primary outcome, 1st primary safety outcome and their components
  - Cox regression – SL - classic approach
  - random survival forest – ML – Tree-based ensemble (bagging)
  - gradient boosted model – ML – Tree-based ensemble (boosting)
  - artificial neural network – DL – multi layer perceptron
- A regression ML-problem to be solved by the following candidate models:
- For 2nd co-primary outcome
  - multiple linear regression – SL - classic approach
  - random forest – ML – Tree-based ensemble (bagging)
  - gradient boosted model – ML – Tree-based ensemble (boosting)
  - artificial neural network – DL – multi layer perceptron

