## ***Model selection***

### **Between model selection**

The best performing model for each of the three ML-problems will be used for further analysis of risk factors. To identify the best model for the regression ML-problem we are going to use **Akaike Information Criteria - AIC** as it is applicable to linear models and non-linear models as well and takes into account model performance and its complexity.

For identifying the best performing time-to-event ML-model we will use the **c-index** and the **Brier Score**.

The information criteria scores will be obtained from applying the model to a hold-out/test dataset of the complete dataset.

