## Handling errors and missing data

For one proband there is a special entry for Variable 'ANG2'. The entry value is 'BLQ' – that stands for Below Limit of Quantitation. Normally those entries will be dealt with as proposed by Bergstrand et al [2]. As we are facing only one entry of this type we are going to set this value to the smallest 'ANG2' value available in the whole dataset.

The remaining dataset has a sample-size of 1585 and missing entries as follows:

- |                          |     |
|--------------------------|-----|
| • Diastolic LA diameter  | 119 |
| • EHRA score at baseline | 97  |
| • MOCA Score             | 42  |
| • LVEF                   | 5   |
| • BMI                    | 4   |

The missing entries will be imputed by SciKit-learn's Iterative Imputer. [3] [4].

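### The SAP specifies its regression models only within an 80/20 train/test scheme and plans no refit on all patients for estimates of association

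*SAP*

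**What the plan says.** Under *Inference Analytics*, the SAP remarks "On the other hand, multiple regression remains the 'gold standard' in the field". It then lists Cox regression (first co-primary and safety outcomes) and multiple linear regression (nights in hospital) as one of four model types to be trained for each problem, beside tree ensembles and a neural network.

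Under *Data preprocessing – All variables*, a 20% hold-out "will be used for evaluating the final model that only relies on the most relevant variables", and that model "has been trained on the remaining 80 % of the dataset". Cox and linear models are not exempted.

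Under *Between model selection*, the best candidate for each problem goes forward to the risk-factor analysis. On the comparison itself the SAP says: "The information criteria scores will be obtained from applying the model to a hold-out/test dataset of the complete dataset". The section on identifying relevant biomolecules then relies on permutation feature importance.

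Two other places bear on the point. *Aim of the study* mentions multivariate analyses first and the machine learning models as an addition, and attaches no split to the former. The list of specific hypotheses says "we developed specific hypotheses that will be tested in" the sub-study, and names neither a model nor a dataset for the tests.

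**The concern.** The aim is to find biomolecules associated with outcome. A hold-out guards against optimism when predictive performance is reported. It does not make a prespecified hazard ratio or regression coefficient more valid. For that purpose it only removes data and makes the estimate depend on which patients the random split happens to set aside.

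The only place where regression models are specified leads into the 80% rule, and nothing in the SAP brings the remaining patients back for estimation. The sponsor treats power as a concern elsewhere: "To increase power and to explore the effect on all events, recurrent events will be analyzed in a separate analysis". Precision given up through the split works against that wish, and it would matter most for the rarer outcomes, such as stroke and major bleeding.

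**Working it through.** The SAP gives no event count, significance level, power target or effect size, so it has no figure of its own to reproduce. What can be computed is the cost of estimating on 80% of the data.

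**Inputs**
- Sub-study size: *Analysis Population* says "These are 1586 patients of which approximately 50% are women", and *Handling errors and missing data* says "The remaining dataset has a sample-size of 1585 and missing entries as follows".
- Training share: 80% (*All variables*).
- Assumed, not in the SAP: two-sided alpha 0.05, baseline power of 80% or 90%, event proportions of 5% to 20%.

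**Step 1: patients.** 0.8 × 1585 = 1268 trained and 0.2 × 1585 = 317 held out. With 1586 the products are 1268.8 and 317.2, so the choice of total does not matter.

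**Step 2: events.** The SAP stratifies the split on the dependent variable. If this refers to the 80/20 split and not only to the cross-validation folds, about one fifth of events fall in the hold-out. A simple random split gives the same on average.

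**Step 3: precision.** The standard error varies as 1/√(events) for a Cox coefficient and 1/√n for a linear one. The ratio of the 80% fit to the full fit is √(1/0.8) = 1.118, so intervals are 11.8% wider.

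**Step 4: power.** Power on 80% of the information is Φ((1.960 + z_power) × √0.8 − 1.960), with √0.8 = 0.894.
- From 80%: (1.960 + 0.842) × 0.894 − 1.960 = 0.546, so power is 70.7%.
- From 90%: (1.960 + 1.282) × 0.894 − 1.960 = 0.939, so power is 82.6%.

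**Step 5: detectable hazard ratio.** Per 1 SD of a biomarker, with 80% power, in a Cox model with no variance inflation from other covariates: HR = exp(2.8016/√events).

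| Assumed event share | Events, all / 80% | Detectable HR, all / 80% |
|---|---|---|
| 5% | 79 / 63 | 1.37 / 1.42 |
| 10% | 158 / 127 | 1.25 / 1.28 |
| 15% | 238 / 190 | 1.20 / 1.23 |
| 20% | 317 / 254 | 1.17 / 1.19 |

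(The 317 events in the last row equal the number of held-out patients only by coincidence.)

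Steps 3 to 5 apply to regression coefficients. If a forest, boosted model or network wins the comparison, it too is trained on 80%, but its loss of precision in ranking biomolecules does not follow this formula and is not quantified here.

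**The case against.** Three stronger readings are tempting, and the SAP does not support them.

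*That the eight specific hypotheses are tested on 80% of patients.* The SAP does not say so. The hypotheses name no dataset, *Analysis Population* covers everyone with biosamples, and *Aim of the study* plans multivariate and recurrent-event analyses with no split. Much of the hypothesis list also lies outside the model list in *Inference Analytics*. Hypotheses 1 to 3 concern recurrent AF, which is defined under the secondary outcomes. Part of hypothesis 4 concerns stroke before baseline. Hypotheses 5 and 6 use ABC scores that are not among the listed predictors. A reader could fairly take the full population as the default for all of these.

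*That Cox and linear regression carry the inference.* The remark on the gold standard suggests it, but the risk-factor step goes to whichever candidate performs best and uses permutation importance. The SAP does not promise to report hazard ratios.

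*That the hold-out has no benefit.* It has one: comparing 24 models and evaluating the final one calls for data not used in training.

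These objections limit the scope of the point but do not remove it. Whichever model wins, the final model is trained on 80%, and no refit is planned. The favourable reading of the hypotheses is an inference by the reader, because the SAP does not state the analysis set. The loss is also moderate: in the table above, the detectable hazard ratio moves by 0.02 to 0.05.

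**Conclusion.** The point holds for any association estimate taken from the trained models. Those estimates would use about 1268 of 1585 patients, with standard errors about 12% larger than necessary. Power would be about 71% where all patients would give 80%, and about 83% where they would give 90%. This is a loss of precision, not a bias.

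For the eight hypotheses and the multivariate analyses in *Aim of the study*, the SAP leaves the dataset open. A loss there is possible but not established. The sample size and the 80% share come from the SAP. The significance level, power baselines and event proportions are assumptions. The 12% figure does not depend on them.

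**What to change.** In *Inference Analytics* and *All variables*, state three things:

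1. The 80/20 split applies only to developing, comparing and evaluating prediction models.
2. The prespecified association models and the models for the specific hypotheses are fitted on all patients with biosamples, and their estimates, intervals and tests are the reported ones.
3. After evaluation, the selected model is refitted on all patients for the reported coefficients, while the c-index and Brier score come from the held-out evaluation.

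The cost is a few lines of text and one refit per model, with no new data. The downside is that the reported performance belongs to the version trained on 80%, so it is slightly conservative for the refitted model. The report should say so.

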## Handling errors and missing data

For one proband there is a special entry for Variable 'ANG2'. The entry value is 'BLQ' – that stands for Below Limit of Quantitation. Normally those entries will be dealt with as proposed by Bergstrand et al [2]. As we are facing only one entry of this type we are going to set this value to the smallest 'ANG2' value available in the whole dataset.

The remaining dataset has a sample-size of 1585 and missing entries as follows:

- |                          |     |
|--------------------------|-----|
| • Diastolic LA diameter  | 119 |
| • EHRA score at baseline | 97  |
| • MOCA Score             | 42  |
| • LVEF                   | 5   |
| • BMI                    | 4   |

The missing entries will be imputed by SciKit-learn's Iterative Imputer. [3] [4].

## Handling unbalanced datasets

We want balanced datasets which means the relation of female to male patients inside the two treatment groups should be equal. Also the number of patients that saw a worsening in heart failure and the ones that did not needs to be balanced. For this purpose, we are going to use Synthetic Minority Oversampling technique – **SMOTE [5]** which uses unsupervised machine learning for clustering to create new augmented samples similar to those of the minority group.

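### SMOTE is used to equalise patients with and without worsening heart failure, an outcome component, with no limit to training data; this distorts absolute risks and the Brier score and invalidates any regression inference run on the augmented data

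*SAP*

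**What the plan says.** The section Handling unbalanced datasets sets two balancing targets. The first concerns sex: "We want balanced datasets which means the relation of female to male patients inside the two treatment groups should be equal". The second concerns an outcome: "Also the number of patients that saw a worsening in heart failure and the ones that did not needs to be balanced". The tool for both is SMOTE, which the section describes as a way "to create new augmented samples similar to those of the minority group". The wording is a commitment, not an option.

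Other sections that bear on this:
- Aim of the study defines the first co-primary outcome as a time-to-event composite. One component is hospitalization "due to worsening of heart failure or" acute coronary syndrome.
- Specific hypotheses lists associations to be tested, including one on heart failure hospitalization.
- Inference Analytics names Cox regression, random survival forest, gradient boosting and a neural network as the time-to-event candidates.
- Between model selection reads "For identifying the best performing time-to-event ML-model we will use the" c-index and the Brier score, obtained on a hold-out set.
- Data preprocessing (All variables) sets a 20% hold-out and a split stratified for the dependent variable.
- Identification of relevant circulating biomolecules names permutation feature importance as the selection tool.

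No section says whether SMOTE comes before or after the split, or whether it stays inside the training folds. None says how predictions return to the true event rate, or what follow-up time and censoring status a synthetic patient receives.

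**The concern.** Balancing a component of the outcome replaces the observed event frequency with an artificial one. Three things are then at stake.

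1. **Absolute risk.** A model trained at about 50% events predicts too high a risk for real patients. The Brier score scores absolute risk, so a model selection criterion is affected.
2. **Inference.** Synthetic records are interpolations of existing patients and carry no new information. A Cox or other regression model that counts them as independent patients gives standard errors that are too small.
3. **Evaluation.** If synthetic records are made before the split, near-copies of training patients sit in the hold-out.

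There is also a gap in definition. SMOTE interpolates covariates and has no built-in way to produce a censored time and status pair, and the SAP supplies no rule. It also names no variant for the one-hot-encoded categorical variables, for which plain interpolation gives fractional values.

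**Working it through.** The SAP states no event rate, alpha or power, so there is no figure of its own to reproduce.

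**Inputs from the SAP.** N = 1585 ("The remaining dataset has a sample-size of 1585 and missing entries as follows"); 14 biomolecules; 80/20 stratified split.

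**Assumptions.** Worsening heart failure in 5%, 10% or 16% of patients; balanced read as 1:1; two-sided 5% level; independent normal noise markers; SMOTE with 5 neighbours.

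**Step 1: how many patients are invented.** With e events and ne = 1585 − e non-events, SMOTE adds ne − e records. The file then has 2·ne records, and the event odds are multiplied by ne/e.

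| Event share | e | ne | Synthetic | Share of file | Share of events synthetic | Odds multiplied by |
|---|---|---|---|---|---|---|
| 5% | 79 | 1506 | 1427 | 1427/3012 = 47% | 1427/1506 = 95% | 19.1 |
| 10% | 158 | 1427 | 1269 | 1269/2854 = 44% | 1269/1427 = 89% | 9.0 |
| 16% | 254 | 1331 | 1077 | 1077/2662 = 40% | 1077/1331 = 81% | 5.2 |

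**Step 2: standard errors.** For a two-group contrast, the ratio of true to reported standard error is about √[(1/e + 1/ne)/(2/ne)] = √[(ne/e + 1)/2]. This gives √10.03 = 3.17, √5.02 = 2.24 and √3.12 = 1.77. A nominal 5% test then rejects a true null with probability 2·[1 − Φ(1.96/ratio)]:
- 5%: 1.96/3.17 = 0.62, giving 54%
- 10%: 1.96/2.24 = 0.88, giving 38%
- 16%: 1.96/1.77 = 1.11, giving 27%

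**Step 3: simulation of Cox models.** Noise markers only, 60 data sets per rate, SMOTE on the training 80%, event times interpolated with the covariates.

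| Event share | Type I error per marker, observed data | Type I error per marker, after SMOTE |
|---|---|---|
| 5% | 4.8% | 57% |
| 10% | 4.3% | 43% |
| 16% | 5.4% | 32% |

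Step 2 predicts the same order of size. After SMOTE, every simulated Cox data set had at least one false positive among the 14 markers. The reference for 14 independent tests is 1 − 0.95^14 = 51%.

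**Step 4: absolute risk and Brier score.** A constant forecast q at true rate p has Brier score p(1 − p) + (q − p)². At p = 0.10, q = 0.10 gives 0.09, and q = 0.50 gives 0.09 + 0.16 = 0.25. Logistic simulation (300 data sets, SMOTE in training only, scored on real hold-out patients) agrees: 0.091 rises to 0.249 with noise only, and 0.088 to 0.222 with two real markers. With noise only, mean predicted risk was 0.47, 0.48 and 0.49 at 5%, 10% and 16%. The bias depends on the model: at true rates of 0.05-0.15, a random forest classifier gave 0.20-0.33 and a boosting classifier 0.10-0.24.

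**Step 5: ranking.** At 10% with two real markers, AUC in real hold-out patients was 0.667 without SMOTE and 0.664 with it. Discrimination is nearly unchanged.

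**Step 6: order of SMOTE and split.** On pure noise, where AUC should be 0.5:
- SMOTE after the split, training only: 0.49-0.53 for all learners tried.
- SMOTE before the split, logistic: 0.56-0.63 at 5-16% events.
- SMOTE before the split, 5-nearest-neighbour: 0.90-0.95; tree-based classifiers: 0.94-0.99.

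In the logistic runs, permutation importance of a noise marker stayed near 0 on real hold-out patients. On the augmented test set it turned positive (0.004-0.010 at 5-16% events).

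**The case against.** The best defence is that SMOTE is meant for training data only. The SAP describes the 20% hold-out before it introduces SMOTE, and scores models on a hold-out of the complete dataset. That suggests a real-patient hold-out but does not say so. If it is the intention, the leakage disappears. The risk bias in Step 4 and the Cox error in Step 3 do not, because both were obtained with training-only SMOTE. The missing rule for follow-up and censoring also remains.

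Four stronger readings are tempting, and the SAP does not support them:
- A reader might infer that predictions become worthless. Calibration is lost, but ranking, and so the c-index, largely survives.
- A reader might infer that noise biomolecules will be selected. The named selection tool is permutation importance, with no p-value rule, and it stayed near 0 for noise on a real hold-out. The false-positive figures apply only to regression p-values and intervals from augmented data. Cox regression and the listed hypotheses make that use possible, but the SAP does not say the tests are run that way.
- A reader might infer an established leak. The order is unstated, so the high AUCs show what one permitted order would do.
- A reader might take a predicted risk of 0.47-0.49 as the general result. It is a logistic figure, and binary logistic regression is not among the listed candidates; the tree classifiers were less biased, though still upward.

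The sex target is a secondary matter. Analysis Population reports that "approximately 50% are women and also around 50% received usual care", and the arms were randomised, so balancing has little purpose. No sex-by-arm figures are given, however, and the sentence may only ask for the same ratio in both arms. That would add few records.

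It can also be argued that resampling is a legitimate choice for a classifier. That stands for a contained sensitivity run, but not for the main time-to-event and association analyses.

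**Conclusion.** The point holds for balancing the outcome. As written, the plan fits models at an artificial event rate of about 50%, biases absolute risks upward by an amount that varies with the model, and distorts one of the two criteria for choosing the time-to-event model. Two consequences are conditional. Type I error of about 32-57% per noise biomolecule arises if Cox regression or the hypothesis tests use augmented data. Inflated performance and permutation importance, with the AUC inflation largest for flexible learners, arise if SMOTE precedes the split.

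The sizes rest on an assumed event share, independent markers, 1:1 balancing and 5-neighbour SMOTE. The survival versions of the forest, boosting and neural network models were not simulated. The direction was the same at every event rate tried, and rarer events raised the type I error. Because the step is a commitment that touches model selection, predicted risk and possibly the hypothesis tests, it should be changed before analysis.

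**What to change.** Remove SMOTE from all time-to-event, regression and association analyses. Fit and evaluate every model on observed patients only, using the stratified split already in the SAP. Drop the sex balancing and keep sex and randomised group as covariates; both are already on the list of clinical parameters.

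If a class-imbalance sensitivity run is wanted, state that weighting or resampling happens inside the training folds only, that predictions are recalibrated to the observed event rate, that evaluation uses an untouched hold-out of real patients, and that no p-values or confidence intervals are reported from augmented data.

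The cost is a change of SAP wording. It removes a processing step and needs no new data.
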